### Approach to qualitative analysis

Interview and focus group transcripts will be imported into NVivo, a qualitative data management and analysis software package. Descriptive content analysis will be used to characterize inductively the issues raised by study participants [87,88]; this process will be performed separately for patients and nurses. Two reviewers, trained in qualitative research methods, will read the transcripts twice to identify pertinent issues and to construct a provisional coding structure before actual coding commences. The two reviewers will then code the transcripts by highlighting units of text that correspond to specific issues, including those reflected in the provisional coding structure. Inter-rater reliability for key issues will be determined. Similar issues will be grouped together under overarching domains. Domain characteristics, including universality (across all informants), idiosyncrasy (unique to one or two informants), and depth (types and richness of subcategories), will be assessed and descriptive statements about each domain will be developed using the patients' words. Reviewers will pay close attention to minority opinions that deviate from the dominant themes and emerging hypotheses [89].

### Cost effectiveness analysis

We will determine the cost-effectiveness ratio for the study intervention from the perspective of the VA health care system. We will account for cessation-related costs incurred during the initial hospitalization and six-month follow-up period in order to estimate the short-term incremental cost per self-reported quitter:

where cost_int _and cost_b _equal the average total direct VA resource cost for the intervention and the control groups, respectively, n_int _is the number of patients exposed to the intervention, and q_int _and q_b _are the six-month quit rates in the intervention and baseline periods, respectively. The denominator reflects change in the number of patients quitting as a result of the intervention. The numerator reflects the change in VA direct costs as a result of the intervention.

Costs related to implementation will include the following: time required for focus groups, initial training, and feedback sessions (both for project staff and nursing staff); nurse training materials, including internet tutorial; time required for CPRS programming to develop nursing reminders and prescription templates; and estimated time spent by peer leaders in coaching staff nurses. We will also include the salary of the full-time central research coordinator and the salary support for the external nurse facilitator, who will provide technical support for peer leaders and nursing staff at all sites. To calculate the costs related to delivery of smoking cessation services, we will estimate the time expended on bedside counseling of smokers by staff nurses, and then multiply this quantity by the average hourly salaries (including benefits) of VA nursing staff, based on VA Human Resources data. We will also track the time spent on telephone counseling, and estimate these costs by multiplying the hourly salary of a quit line counselor by the number of hours spent on telephone counseling. The costs of pharmacotherapy will be based on the quantity dispensed and the average wholesale price for each product (generic transdermal NRT, bupropion, and/or second-line drug therapies). We will also include the costs of patient education materials (brochures and educational video). For patients in each period, we will estimate the cost of outpatient visits for cessation counseling and/or smoking cessation pharmacotherapy (including management of adverse reactions) during six-month follow-up (by identifying cessation-related office visits and multiplying by the average cost for a physician visit).

To assess the robustness of the incremental cost per quitter to changes in effectiveness, we will perform one-way sensitivity analyses over plausible ranges of cost parameters and the six-month quit rate. The uncertainty of the incremental cost per quitter will also be estimated using non-parametric bootstrapping (with 1,000 replications), based on random sampling with replacement of a number of participants in the trial [90].

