### Sample size calculations

Based on the volume of admissions at each study hospital, we plan to screen 7,548 potential subjects who are hospitalized on medical wards for greater than 24 hours during the enrollment period at the four sites. Based on chart review, we estimated smoking prevalence at each site (weighted average = 23%, range 17 to 32%), and determined that approximately 80% of identified smokers will be eligible to participate in the proposed trial. Assuming that 84% of eligible patients consent to participate (based on a recent VA smoking cessation study [47]), we would expect 1,000 subjects to enroll in the study (500 baseline, 500 intervention). Pooling the control group data from studies of general medical inpatients, we estimate a 12% quit rate at six-months (seven-day PPA). Thus, a study sample of 1,000 patients will have 83% power to detect a seven percentage-point difference between periods in six-month quit rates. This effect estimate is consistent with that observed in prior hospital intervention trials that employed a sustained relapse prevention component [16,20,21]. Based on chart reviews at two study sites, we estimate that 12 and 13% of inpatients during the baseline period will be referred for cessation counseling and will receive recommended pharmacotherapy, respectively. The projected study sample will have 81 and 83% power to detect a seven percentage-point difference in these process measures, respectively. These power calculations are based on a hierarchical linear model, with nurse treated as a random factor (and patient outcomes are clustered within nurse); intracluster correlation (ICC) was estimated to be 0.05 for assistance in quitting (which includes offering of pharmacotherapy and arranging follow-up), and 0.01 for abstinence, based on data from the AHRQ Smoking Cessation Guideline Evaluation Trial [77].

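### The cost-per-quitter numerator includes the full-time research coordinator's salary without separating research time from implementation time, so the ratio is likely to be overstated unless research time is removed

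*Protocol article*

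**What the plan says.** All the text on this point is in the protocol article, under Cost effectiveness analysis, apart from the planning figures under Sample size calculations.

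- Perspective: "We will determine the cost-effectiveness ratio for the study intervention from the perspective of the VA health care system".
- Scope of costs: "We will account for cessation-related costs incurred during the initial hospitalization and six-month follow-up period".
- Numerator: "The numerator reflects the change in VA direct costs as a result of the intervention".
- Denominator: "The denominator reflects change in the number of patients quitting as a result of the intervention".
- The list of implementation costs opens with "Costs related to implementation will include the following: time required for focus groups, initial training, and feedback sessions". It goes on to training materials, record-system programming time and peer-leader coaching time.
- The next sentence is the one at issue: "We will also include the salary of the full-time central research coordinator and the salary support for the external nurse facilitator". It ends with a clause on the purpose of the post or posts: "who will provide technical support for peer leaders and nursing staff at all sites".

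The article gives no salary, no period over which it is charged, no effort share and no description of the coordinator's duties. It plans one-way sensitivity analyses over cost parameters and the quit rate, and a bootstrap. No analysis that leaves out research staff is named.

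**The concern.** The article states a costing rule here, and the rule sits badly with its own definition of the numerator. A salary belongs in that numerator only so far as the work is done because of the intervention. A post titled research coordinator, full-time and central, in a study that collects data on two cohorts at four sites, plausibly includes work that a VA hospital adopting the program would not need to buy.

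The ratio is meant to tell the VA what an additional quitter costs in the short term, and the Discussion offers the results to VA decision makers. Research cost counted as program cost would make the program look poorer value than it is. Cost-effectiveness is one of the key secondary aims. The abstinence and process-of-care endpoints are not affected.

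**Working it through.** **Is the full salary the natural reading?** Three features of the section point that way.

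1. Most other labour is costed by time: focus groups, training and feedback, programming, peer-leader coaching, bedside counselling and telephone counselling. The coordinator enters as a salary.
2. Within one sentence, the coordinator has a salary and the facilitator has salary support. That contrast suggests whole against partial.
3. The sentence follows directly on the implementation costs, which arise only with the intervention. Where the section means both periods, as for outpatient visits, it says so.

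These are grounds for a reading. They are not a statement in the text.

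**Size.** The article gives no cost or cost-per-quitter figure, so there is nothing to reproduce. Its displayed formula is not legible in the text available, so I work from the verbal definitions:

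cost per quitter = (change in VA direct cost) / [n_int × (q_int − q_b)]

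If a research-only amount R is left in the intervention's costs, the ratio rises by

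R / [n_int × (q_int − q_b)]

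Inputs, all from Sample size calculations:

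- n_int = 500 ("we would expect 1,000 subjects to enroll in the study (500 baseline, 500 intervention")
- q_b = 12%
- planned difference = 7 percentage points, so q_int = 19%

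Extra quitters = 500 × (0.19 − 0.12) = 35.

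Rise per $10,000 of research-only salary = 10,000 / 35 = $286.

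The figure depends on the effect actually achieved:

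| Difference in quit rate | Extra quitters | Rise per $10,000 |
|---|---|---|
| 3 points | 15 | $667 |
| 5 points | 25 | $400 |
| 7 points (planned) | 35 | $286 |
| 10 points | 50 | $200 |

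**Illustration with assumed figures.** None of the following is in the article. Assume salary with benefits of $40,000 to $80,000 a year, charged for 0.5 to 3 years, at 35 extra quitters.

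- Research share 0%: $0.
- Research share 50%: from 40,000 × 0.5 × 0.5 / 35 = $286 to 80,000 × 3 × 0.5 / 35 = $3,429 per quitter.
- Research share 100%: from 40,000 × 0.5 / 35 = $571 to 80,000 × 3 / 35 = $6,857 per quitter.

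If the same research cost were booked equally to both periods, it would cancel and the rise would be $0.

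**Do the planned safeguards deal with it?** A one-way sensitivity analysis varies a parameter around the base case. It could be made to cover this salary, but the article does not say so, and the base case would keep the misallocated part. The bootstrap resamples participants, so it does not address whether a fixed salary belongs in the numerator.

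**The case against.** A reader might infer that the whole salary is charged to the intervention side alone, so that research cost is certainly counted as intervention cost and the ratio is certainly too high. The documents do not go that far, for these reasons:

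- The text says neither that the whole salary is charged nor that it is charged only to the intervention. Costs are defined for both periods, and equal booking would remove the effect.
- The sentence ends with a reason tied to implementation, technical support for peer leaders and nurses. By grammar this belongs to the facilitator, but it may extend to the coordinator.
- The obvious research tasks are given to others. Under Screening and recruitment and Patient-level data, a site research assistant screens patients and does the enrolment and pre-discharge interviews, and research interviewers make the follow-up calls. None of these posts is named in the cost list, so the plan does not sweep research labour in general into the numerator.
- Because the sites are staggered, a central post can be supporting implementation at one site while another is still in its baseline period. Work done during a baseline period is therefore not necessarily research work.
- How one post is apportioned is a detail that a condensed article may leave to a fuller document.

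The first four objections stand and limit the point to a conditional one. The last does not remove it: the article does not leave the item open but names the salary as a cost to include, next to a numerator definition that it may not meet. If the technical-support clause does cover the coordinator, it justifies the share of time spent on support and no more.

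**Conclusion.** The point holds in conditional form. The coordinator's salary is included with the implementation costs with no separation of research from implementation time, and this does not fit a numerator limited to costs resulting from the intervention. That much can be said with confidence.

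The likely direction is upward, since any research-only part charged to the intervention raises the cost per quitter. The rate of $286 per $10,000 assumes 500 intervention patients and the planned 7-point difference. The total is unknown. The illustrative dollar ranges rest wholly on assumed salary, duration and research share, and should not be read as an estimate for this study. A definite overstatement, or one equal to the whole salary, is not supported.

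**What to change.** Replace the salary item with a rule along these lines: *the coordinator's time spent on implementation support (training, feedback, and technical support to peer leaders and nursing staff) will be costed at hourly salary with benefits; time spent on research tasks such as recruitment, consent, follow-up and data management will be excluded.* This puts the coordinator on the time basis already used for the nursing staff and quit line counsellors.

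Take the hours from a simple time log, or from a percentage split agreed before the cost results are seen. Classify time by task and not by calendar period, because the staggered sites mean that baseline and intervention work can overlap for a central post.

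Report the ratio on this basis as the base case, and give the ratio with the full salary as a named sensitivity analysis, so that a reader can see how much the choice matters.

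The cost is a little record keeping for one post and a sentence or two in the cost section.

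### The cost-per-quitter numerator is defined as direct VA cost, but drugs are priced at average wholesale price and the research coordinator's salary has no stated implementation share

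*Protocol article*

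**What the plan says.** All of this stands in the protocol article, Methods, Cost effectiveness analysis.

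The standard is set first: "We will determine the cost-effectiveness ratio for the study intervention from the perspective of the VA health care system". The two cost terms "equal the average total direct VA resource cost for the intervention and the control groups, respectively", and "The numerator reflects the change in VA direct costs as a result of the intervention".

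The inputs follow:

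- **Drugs.** "The costs of pharmacotherapy will be based on the quantity dispensed and the average wholesale price for each product".
- **Nurse time.** Bedside counseling hours are multiplied by the "average hourly salaries (including benefits) of VA nursing staff, based on VA Human Resources data".
- **Central staff.** "We will also include the salary of the full-time central research coordinator and the salary support for the external nurse facilitator", followed by the clause "who will provide technical support for peer leaders and nursing staff at all sites".
- **Training and feedback.** Time in focus groups, training and feedback sessions is already charged for project staff as well as nursing staff.

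One-way sensitivity analyses over plausible values of the cost parameters and the quit rate are planned, together with a bootstrap that resamples participants.

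**The concern.** The section sets a test for its numerator, namely direct cost to the VA caused by the intervention. Two of the inputs it then fixes are not shown to meet that test.

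Average wholesale price is a market price. Nothing in the article says that it equals, or stands in for, what the VA spends on these drugs. Labor, by contrast, is taken from the VA's own records. An error in unit price would matter little if both periods dispensed the same amount, but Hypothesis 1b predicts more prescribing in the intervention period, so the error carries into the cost difference.

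The coordinator's post is, by title, a research post. Most other staff items are entered as time spent on a named activity, and the nurse facilitator is entered as salary support. The coordinator is entered as a salary, with no rule for separating implementation support from research. Any research-only part would not be bought to run the program and is not caused by it. Coordinator time at training or feedback sessions could also be counted twice, once as project-staff time and once as salary.

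Short-term cost-effectiveness is a key secondary aim, and the Discussion offers the results to VA decision makers with system-wide use in view. A ratio that mixes VA costs, market prices and possibly research overhead does not answer their question cleanly.

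**Working it through.** The article states no price, salary or cost per quitter, so there is no figure to reproduce. What can be computed is how far each input moves the ratio.

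**Inputs**

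- Intervention patients: 500 (Sample size calculations).
- Six-month quit rates: 12% at baseline and a seven-point difference, hence 19% (same section).
- Receipt of recommended pharmacotherapy: 13% at baseline, with a seven-point difference as the detectable change (same section).
- Salaries and drug prices: not given. Every dollar value below is an assumption or a rate per assumed unit.

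**Ratio**, rebuilt from the verbal definitions because the displayed formula is not in the text available:

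ratio = n_int × (cost_int − cost_b) / [n_int × (q_int − q_b)]

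Denominator: 500 × (0.19 − 0.12) = 35 extra quitters.

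**Drug price.** If incremental drug cost is misstated by $1 per intervention patient, the ratio shifts by 500 × $1 / 35 = $14.29 per extra quitter. This equals $1 / 0.07, so it does not depend on cohort size. An assumed misstatement of $5 to $50 per patient gives $71 to $714, in either direction.

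To relate this to a course of treatment, assume that the quantity per treated patient is the same in both periods and that uptake rises from 13% to 20%. A price wrong by $d per course then misstates incremental cost by 0.07 × d per patient, and the ratio by 0.07 × d / 0.07 = $d per extra quitter. A $50 error per course is therefore a $50 error per extra quitter. The upper end of the $71 to $714 range would need a much larger rise in dispensing or a large price gap.

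**Coordinator salary.** Each $10,000 of research-only salary left in the numerator adds $10,000 / 35 = $286 per extra quitter. For an assumed $50,000 charge:

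| Research-only share | Excess per extra quitter |
|---|---|
| 0% | $0 |
| 25% | $357 |
| 50% | $714 |
| 100% | $1,429 |

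For assumed charges of $30,000 to $100,000, the ceiling (all of it research-only) is $857 to $2,857.

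**Dependence on the effect.** Both rates vary inversely with the quit-rate difference. If the true gain were 3.5 points (17.5 extra quitters), they would double to about $29 and $571.

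**The case against.** **The planned sensitivity analyses cover it.** Drug price and salary are cost parameters, so the one-way analyses could vary both. This softens the point. But they name neither a VA price nor a version without research time, and they leave the base case as it is. The bootstrap resamples participants, so it cannot reflect error in a fixed unit price or salary.

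**The coordinator may be an implementation cost.** The technical-support clause sits nearest to the facilitator but can be read as covering both posts, in which case part or all of the salary belongs in the numerator. That stands: the fault is the missing split, not the inclusion as such. A reader might infer that the coordinator handles recruitment, consent or follow-up. The article does not say so. It gives screening and in-hospital interviews to site research assistants, and follow-up calls to research interviewers. It also does not say that 100% of the salary is charged; full-time describes the post.

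**The size is unknown.** This is also right. A reader might conclude that the ratio is necessarily overstated, but with no wholesale or VA price in the article, the sign of the drug-price error cannot be shown.

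**The denominator.** A reader might also infer that raw period quit rates are used, at odds with the adjusted primary analysis. The text defines the rates only by period and does not call them unadjusted, so this is not supported.

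**An article condenses.** Apportionment detail may well be in the full protocol. That weakens the salary point. It does not touch the drug price, which the article fixes explicitly.

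**Conclusion.** The point holds in a limited form. The firm part is textual: the section promises direct VA cost and then prices drugs from a source that it does not connect to VA cost, while using VA data for nurse labor. The second part, the coordinator's salary without a stated split, is a gap that may let research cost into the base case.

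At the design values the leverage is about $14 per extra quitter for each $1 per patient of misstated incremental drug cost, and about $286 per extra quitter for each $10,000 of research-only salary. These rates assume 500 intervention patients and the planned seven-point gain. The actual error cannot be computed: the drug-price part has unknown sign and size, and the salary part could be anywhere from zero up to the full amount charged. With only 35 extra quitters expected, fixed costs have the stronger leverage.

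The abstinence and process-of-care analyses are unaffected. This is a worthwhile correction to a secondary aim and no threat to the trial's main conclusions.

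**What to change.** In the base case:

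- Multiply the quantity dispensed by VA acquisition cost, taken from VA pharmacy records.
- Charge only coordinator time spent on implementation, excluding any already counted as project-staff time in focus groups, training and feedback sessions.

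Report average wholesale price and the full coordinator salary as named sensitivity cases, so that readers can see how much each choice moves the ratio.

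The cost is a change of price source and a simple time log. The downside is that the coordinator's split will be partly self-estimated; the full-salary case bounds the effect of that.

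### The cost-effectiveness analysis is defined on VA direct costs, but its base case prices drugs at average wholesale price, which the protocol does not show to be what the VA pays

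*Protocol article*

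**What the plan says.** All the relevant rules stand in the protocol article, Cost effectiveness analysis.

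- Perspective: "We will determine the cost-effectiveness ratio for the study intervention from the perspective of the VA health care system".
- Cost terms: the two group costs in the ratio "equal the average total direct VA resource cost for the intervention and the control groups".
- Numerator: "The numerator reflects the change in VA direct costs as a result of the intervention".
- Drug price: "The costs of pharmacotherapy will be based on the quantity dispensed and the average wholesale price for each product". The products listed are generic transdermal nicotine replacement, bupropion and second-line drugs.
- Nursing time: hours are multiplied by "average hourly salaries (including benefits) of VA nursing staff, based on VA Human Resources data".
- Uncertainty: "we will perform one-way sensitivity analyses over plausible ranges of cost parameters and the six-month quit rate". A non-parametric bootstrap of participants with 1,000 replications is also planned.

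Two other sections bear on the point. Hypothesis 1b (Study aims) expects more intervention than usual-care patients to be prescribed pharmacotherapy. Sample size calculations puts baseline pharmacotherapy at 13% with a detectable rise of seven percentage points, and for abstinence gives "83% power to detect a seven percentage-point difference between periods in six-month quit rates".

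**The concern.** The section first says whose cost is being measured and then prices one component from a source not tied to that payer. Nothing in the article says that the VA buys at average wholesale price, gives a discount or conversion, or explains why the reference price is an acceptable stand-in. This is a stated rule that does not match the stated quantity. It is not a detail that a condensed article has left out: a fuller document would have to change or justify the rule, not merely complete it.

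It matters because more drug use is one of the intervention's intended effects. The numerator is a difference between periods, so a unit-price error multiplies the extra drug use and passes into cost per quitter. Short-term cost-effectiveness is a listed secondary aim, and the Discussion names VA decision makers among the users of the results. They need the VA's cost.

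**Working it through.** **Plan's own figure.** None exists to reproduce. The article gives no drug price, cost total or cost per quitter.

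**Form of the ratio.** The displayed equation is missing from the text as read. From its defined terms it is taken as

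n_int × (cost_int − cost_b) / [n_int × (q_int − q_b)] = (cost_int − cost_b) / (q_int − q_b).

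**Inputs**
- Rise in the proportion treated with drugs, dp = 0.07, from 13% to 20% (Sample size calculations).
- Rise in the six-month quit rate, dq = 0.07 (same section).
- Intervention patients: 500 (same section).
- D: drug cost per treated patient at average wholesale price. Not given; results are shown per $100.
- f: VA price as a fraction of average wholesale price. Not given; assumed range 0.25 to 1.25, with one f for all products.
- Mean quantity dispensed per treated patient is taken as equal in the two periods.

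**Step 1: does the error cancel?** Suppose each treated patient's drugs are mispriced by $100. The error in mean cost is 0.20 × $100 = $20 in the intervention period and 0.13 × $100 = $13 at baseline. The numerator is therefore off by $20 − $13 = $7 per enrolled patient, not zero.

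**Step 2: effect on cost per quitter.** $7 / 0.07 = $100. In totals, 500 × 0.07 = 35 extra treated patients × $100 = $3,500, divided by 500 × 0.07 = 35 extra quitters, again $100. More generally, each $1 of error per enrolled patient in the incremental drug cost moves cost per quitter by 1 / 0.07 = $14.29.

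**Step 3: dependence on f.** The drug part of cost per quitter is D × dp / dq at average wholesale price and f × D × dp / dq at the VA price. The ratio of the two is 1/f, and the error is D × (1 − f) × dp / dq. With dp = dq and D = $100:

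| f | Drug part at VA price | Drug part at average wholesale price | Error | Factor 1/f |
|---|---|---|---|---|
| 0.25 | $25 | $100 | +$75 | 4.00 |
| 0.50 | $50 | $100 | +$50 | 2.00 |
| 0.75 | $75 | $100 | +$25 | 1.33 |
| 1.00 | $100 | $100 | $0 | 1.00 |
| 1.25 | $125 | $100 | −$25 | 0.80 |

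**Step 4: effect on the whole ratio.** If drugs make up a share s of the incremental cost as the plan prices it, the ratio at VA prices equals the planned ratio × [1 − s(1 − f)]. Neither s nor f is in the documents, so this cannot be evaluated.

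**Step 5: would the planned uncertainty analyses reveal it?** The bootstrap resamples participants, and every replicate carries the same unit price, so its interval is centred on the same mispriced figure. The one-way sensitivity analysis could include drug price, but the text names neither drug price nor a VA value, and it leaves the base case unchanged.

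**The case against.** The strongest reply is that no bias has been shown. The documents contain no VA price, so f could be 1 and the mismatch would then have no numerical consequence. A reader might infer that average wholesale price overstates what the VA pays and so makes the intervention look less cost-effective than it is. The documents do not support that: they fix neither the size nor the direction, and at f above 1 the error runs the other way. This part of the objection stands, and the point is worded conditionally for that reason.

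Second, a drug price is a cost parameter, so the planned one-way analysis may already cover it, and the ranges could reasonably sit in a fuller document. That is fair as to the ranges. It does not settle which price carries the headline result.

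Third, drugs are not the only item without a stated VA source: quit line counselor salary and the average cost of a physician visit have none either. That also stands, so the contrast with nursing time should not be pressed as though drugs were the sole exception. The difference is that those sources are left open, whereas for drugs a general market price is named.

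Fourth, the sum may be small. At the planned seven-point rise, a $100 error adds $3,500 to a total that also carries coordinator and facilitator salary, training, programming and counseling. Larger shifts would follow from a bigger rise in drug use, but the documents give no rise beyond seven points. Nor do they show that VA prices sit in the same records as quantity dispensed, so the ease of obtaining them should not be assumed.

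**Conclusion.** The point holds in a limited form. The named drug price does not match the perspective and numerator that the same section defines, and the protocol does not justify it as a proxy. If the VA price is f times average wholesale price, the drug component of incremental cost is wrong by a factor of 1/f. At the protocol's own planning differences, each $100 of mispricing per treated patient moves cost per quitter by $100.

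This rests on the ratio as rebuilt from its defined terms, on equal quantities per treated patient in both periods, and on the seven-point differences being realised. The actual error in the reported ratio cannot be stated, because neither f nor the drug share of total cost is given. The abstinence, process-of-care and nurse-attitude analyses are untouched. The change is worth making because the base case should measure the quantity that the section defines.

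**What to change.** In Cost effectiveness analysis, replace the drug-price rule so that the base case values dispensed quantities at VA acquisition cost per unit, and name the source and price date. Keep average wholesale price as one named value in the planned one-way sensitivity analysis. If VA prices cannot be obtained, say that average wholesale price is used as a proxy for VA cost, give the reason, and vary it explicitly over a stated range that allows for VA prices both below and above it.

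The cost is one or two sentences of text and the work of obtaining VA unit prices for a small number of products. No change to the design, sample size or patient data collection is needed.
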